### Outcomes

The primary outcomes are:

- Consent to study of eligible patients- Young people participants willing to be randomised in a main RCT- Fidelity to COPING- Participant adherence to COPING- Participant follow-up rate of outcome measures- Acceptability of COPING to participants and GPs- Deliverability of COPING

The secondary outcomes are:

- Response rates of invited practices to participate- Identification of patients at sites- Proportion of identified patients eligible for study inclusion- Participant recruitment uptake through recruitment strategies- Willingness of GPs to be randomised in a main RCT- Assessment of outcome measure to use as the primary outcome in a main RCT- Proportion of participants with repetition of self-harm- Participant attrition, follow-up, and withdrawal rates

This feasibility study is not designed to evaluate health outcome measures formally. We will collect clinical effectiveness data that may support the justification for a future main trial. These data may also be used to decide which outcomes could and should be collected in a future RCT, and to estimate parameters required to calculate the sample size calculation for a fully powered RCT.

The progression decision-making process will include consideration of the feasibility study progression outcomes (aligned to the primary outcomes: see
Table 1) with the study steering committee (SSC), patient and public involvement (PPI) group, and research team to consider if moving to a fully powered RCT is feasible.

**Table 1. T1:** Progression criteria for a future main trial.

Criteria	Go – proceed to RCT	Amend – proceed with minor changes	Stop – do not proceed unless major changes are possible
Consent to study in eligible patients	>30%	15–30%	<15%
Young people participants willing to be randomised in a future RCT	>85%	60–85%	<60%
Fidelity to COPING treatment checklist	>67%	40–67%	<40%
Participant adherence to COPING	>67%	40–67%	<40%
Participant follow-up rate of outcome measures	>80%	50–80%	<50%
Acceptability of COPING to GPs and patients	COPING judged very acceptable by GPs and patients by qualitative data	COPING judged acceptable by GPs and patients by qualitative data	COPING judged somewhat acceptable by GPs and patients by qualitative data
Delivery of COPING by GPs	Delivery of COPING judged strongly feasible by qualitative data	Delivery of COPING judged feasible by qualitative data	Delivery of COPING judged possibly feasible by qualitative data

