### Sample size

Non-randomised COPING delivery:

We will aim to recruit approximately six general practice sites and around 3 GPs at each site. The incidence rate of recorded self-harm in young people in general practice is around 60 per 10,000 person-years
^
23
^. This equates to 60 per 1,000 for the 16–25 age group over one year. If half are eligible for the study (30 per 1,000) and two-thirds of those are identified by our recruiting methods (20 per 1,000) then in a typical GP practice (assumed 6,000 registered patients of which 900 (15%) are in the 16–25 age group) about 18 eligible young people will contact their GP practice per year after self-harm (1.5 eligible young people per practice per month). If six practices are recruited to take part, nine young people would be expected to be eligible per month, and around 104 (the target eligible population size) over about 12 months. From this number (n=104) we would expect to recruit 31 participants (30%) (fulfilling the Go signal for progression for the recruitment criterion – see
Table 1) into the study.

The sample size of n=31 participants is required to test against the feasibility progression criteria (specifically the cut-off for a STOP signal) with at least 90% power, using the normal approximation method for binary outcomes using a 1-sample 1-sided test with 5% alpha (type I error) using the approach of Lewis
*et al.*
^
24
^ In line with the recommendation of the CONSORT-extension for randomised pilot and feasibility studies this provides necessary justification for the sample size requirement for the evaluation of the progression criteria for this feasibility study
^
25
^.

GP survey:

A sample of 100 GPs across England will be surveyed to elicit GP views about a future main RCT of COPING. Achieving 100 GP responses from a convenience sample has recently been shown to be achievable
^
26

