### Statistical methods

Participant characteristics, eligibility and recruitment rates, attendance at second COPING consult, baseline and follow-up questionnaire response rates, GP survey responses, and resource use will be reported descriptively using SPSS (Statistical Package for the Social Sciences) v27 or later
^
30
^. Continuous variables (e.g., age) will be reported with means and standard deviations or median (IQR) as appropriate and categorical variables (e.g., sex) will be reported with frequencies and percentages.

Analysis of outcomes against the predefined feasibility study progression criteria will include estimated percentages with 95% confidence intervals (e.g., rates of consent or willingness to be randomised). Participant follow-up rate of outcome measures will be assessed as the total completions attained of the SBQ-R measure at all three timepoints as a percentage of the possible denominator (n=93). Participant adherence to the COPING intervention will be ascertained by examining the proportion of participants who attend for the 2nd COPING consult. Participant PHQ-9 and SBQ-R scores at baseline and follow-up timepoints will be compared using paired t-test (if normal distribution) or Wilcoxon paired rank test
^
31
^.

Fidelity of the COPING intervention will be measured retrospectively by reviewing CRF data completed by site GPs against the COPING delivery checklist. Overall fidelity will be calculated as a percentage of the participants where the number of COPING items successfully delivered is at least three out of five (from the five BCTs targeting the young person’s target behaviour), as agreed with the SSC.

We will investigate how much missing data there is in this study to inform the planning of a future RCT. This will occur at two levels: i) observe how much loss to follow-up there will be (participant attrition or withdrawal), and ii) assess completion rates, including missing data for specific data items, of follow-up questionnaires.

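### The one-sided 5% test that justifies n=31 does not reappear in the analysis section or Table 1, and the natural readings of those sections do not deliver both the stated 5% error and 90% power

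*Protocol article*

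**What the plan says.** Three places in the protocol article bear on this.

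- **Sample size.** The figure of 31 is "required to test against the feasibility progression criteria (specifically the cut-off for a STOP signal) with at least 90% power". The method is the normal approximation for a binary outcome, with a one-sample one-sided test at 5%. The section presents this as the justification for evaluating the progression criteria.
- **Statistical methods.** "Analysis of outcomes against the predefined feasibility study progression criteria will include estimated percentages with 95% confidence intervals". The sidedness of the interval is not given. No test, null value or rule connecting an interval to a progression band is named.
- **Outcomes, Table 1.** Five quantitative criteria have Go, Amend and Stop bands, the last headed "Stop – do not proceed unless major changes are possible". The Stop/Go limits are 15/30% for consent, 60/85% for willingness to be randomised, 40/67% for fidelity, 40/67% for adherence and 50/80% for follow-up. The table does not say whether a band applies to the observed percentage or to a confidence limit. The text above it says that the steering committee, the PPI group and the research team will consider these outcomes together.

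**The concern.** A sample size justified by a test carries its error rate and power only if that test, or its equivalent, is used on the data. Here the design test is one-sided at 5%. The matching interval is a two-sided 90% interval or a one-sided 95% limit. The section that describes the analysis names 95% intervals, which by convention are two-sided and correspond to a one-sided 2.5% test. Table 1 on its face sorts the observed percentage.

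Progression is the purpose of the study, and the Discussion says that the criteria will determine whether a main trial is justified. A reader who takes the Sample size section at its word will believe that a rate at the STOP limit has only a 5% chance of being classed as better than STOP. If the bands are applied to observed percentages, a result compatible with STOP can be reported as needing only minor changes.

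**Working it through.** **Inputs.** n = 31 for willingness, fidelity and adherence; n = 104 eligible patients for consent (Sample size). The follow-up denominator is given as 93 completions (Statistical methods), but these are three repeated measures on 31 people, so 31 is used here. The null p0 is the STOP limit. The alternative p1 is taken as the GO limit; this is an assumption, since the article does not state the alternative.

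**Step 1: reproduce n=31.** With q = 1 − p,

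n = [(1.645·√(p0q0) + 1.2816·√(p1q1)) / (p1 − p0)]²

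For fidelity and adherence (0.40 v 0.67): [(1.645×0.4899 + 1.2816×0.4702)/0.27]² = 27.2. With continuity correction, (n/4)·[1 + √(1 + 2/(n(p1 − p0)))]² = (27.2/4)·[1 + √(1 + 2/7.35)]² = 30.8, so 31. The other criteria need 29.4 (willingness), 23.0 (follow-up at one time point) and 67.8 (consent, with 104 available). So 31 is the continuity-corrected figure for the most demanding criterion measured on participants, and it is correct for the test named.

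**Step 2: bands read on the observed percentage.** Exact binomial probabilities of not being classed as STOP:

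| Criterion | Smallest count outside STOP | True rate at STOP limit | True rate at GO limit |
|---|---|---|---|
| Fidelity, adherence | 13/31 | 48.0% | 99.9% |
| Willingness | 19/31 | 52.0% | >99.9% |
| Follow-up (n=31) | 16/31 | 50.0% | >99.9% |
| Consent | 16/104 | 49.8% | >99.9% |

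The 5% error is lost; the power to leave STOP is not.

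**Step 3: a two-sided 95% interval must exclude the STOP limit.** The nominal one-sided error is 2.5%. Power = Φ{[(p1 − p0)√n − c − z·√(p0q0)] / √(p1q1)}, with z = 1.96, and c = 0 (uncorrected) or 1/(2√n) (continuity-corrected).

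Fidelity and adherence: (0.27×5.568 − 1.96×0.4899)/0.4702 = 1.155, giving 87.6%. Subtracting c = 0.090 from the numerator gives 0.964, so 83.2%. The design test (z = 1.645) gives 93.1% and 90.2%.

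| Criterion | Uncorrected | Continuity-corrected | Exact limits |
|---|---|---|---|
| Fidelity, adherence (n=31) | 87.6% | 83.2% | 80.8% (19/31 needed) |
| Willingness (n=31) | 88.7% | 83.1% | 82.7% (25/31 needed) |
| Follow-up (n=31) | 95.8% | 93.3% | 92.5% |
| Consent (n=104) | 96.5% | 95.6% | 95.3% |

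To keep 90% power for fidelity and adherence with a two-sided 95% interval, the Step 1 formula with 1.96 gives 33.5 (34) uncorrected, or 37.1 (38) with the correction.

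**Step 4: where the bands and the test disagree.** For fidelity or adherence, 13/31 to 17/31 (42% to 55%) falls in the Amend band. Exact one-sided p-values against 40% run from 0.48 at 13/31 to 0.068 at 17/31. At 17/31 the uncorrected z is (0.548 − 0.40)/0.088 = 1.69, which exceeds 1.645; the continuity-corrected z is (17 − 0.5 − 12.4)/√(31×0.24) = 1.50, which does not. So 13–16 fail by any of these methods, and 17 depends on the method.

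**The case against.** The strongest reply is that this is a gap in a condensed article. The Sample size section does say that the study will test against the criteria and cites a published approach. The analysis sentence says what will be included, which need not be everything. A SAP that is not shown may contain the rule. The interval's sidedness is not stated, and a one-sided 95% limit would match the design test exactly. The decision is a joint judgement that also weighs two qualitative criteria, so a mechanical rule may never have been intended.

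Much of that stands, and it limits what can be claimed. A reader might infer that the test has been abandoned, or that Table 1 decides on point estimates. The article says neither: the first cannot be shown from it, and the second is the natural reading of a table that is silent. A reader might also infer that neither the error nor the power holds. That is wrong for power: on observed percentages the chance of leaving STOP at the GO limit is about 99.9%, and with two-sided 95% intervals consent and follow-up stay above 90%. The willingness shortfall also depends on the interval. An uncorrected score or Wald 95% interval excludes 60% from 24/31 upwards, the same count as the one-sided 5% test, and its exact power is 91.8%. For fidelity and adherence the same intervals need 18/31, with exact power 89.3%.

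An exact 18/31 threshold should not be imposed as though it were the design rule. The article names the normal approximation, and the exact test at 18/31 has power of 89.3%, just under the target.

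What the reply does not remove is that the article itself fixes 95% intervals as the described analysis and quotes an error rate and power for something else.

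**Conclusion.** The point holds as a mismatch between three sections. It is not an error in N, which reproduces. Under the two natural readings, the 5% error and the 90% power do not hold together as stated. On observed percentages the error is about one half and the power is ample. With two-sided 95% intervals the error is nominally 2.5%, and the planning power for fidelity, adherence and willingness falls to between about 81% and 89%.

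This rests on three assumptions: the GO limit as the alternative (supported by its reproducing 31), two-sided intervals, and full denominators of 31 and 104. Willingness is asked only in the eight-week questionnaire, so its denominator may be smaller. If one-sided 95% limits were meant and are compared with the STOP cut-offs, the mismatch disappears, but the article would need to say so. It is worth correcting because the stated error rate supports the study's main decision.

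**What to change.** In Statistical methods, and in a note under Table 1, state that each quantitative criterion is tested against its STOP cut-off with the one-sided 5% test used for the sample size. Equivalently, compare the cut-off with the lower limit of a two-sided 90% interval, or a one-sided 95% limit, built by the same method. Use the same normal approximation, say whether it is continuity-corrected (the version that gives 31), and use the actual denominator. Report an Amend estimate that does not reject the STOP value as not having excluded STOP, so that the committee sees this when it considers progression.

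Alternatively, keep two-sided 95% intervals and restate the power as about 81–89% for fidelity, adherence and willingness, depending on method.

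Either change is wording only and leaves n=31 as it is. The cost of the first is that some low Amend results, such as 13/31 to 16/31 for fidelity or adherence, will read less favourably.

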### Recruitment

General practices in the National Institute for Health and Care Research Local Clinical Research Network (CRN) West Midlands will be invited to participate in the study by email. Practices who agree to participate will receive a local information pack, a site initiation visit, COPING training, and an investigator site file. Recruited practices therefore become study sites. Each site will have a designated principal investigator (PI), and each site PI will identify GPs who want to deliver COPING to participants. GPs who use COPING with participants become study co-investigators

Patient recruitment to self-harm clinical trials in NHS general practice is untested and thus we will test three participant recruitment strategies which have been informed by the study’s PPI group:

1) General practice electronic healthcare records: practice database searches will be developed for sites to use to identify potentially eligible patients.2) Study advertisement: recruitment posters will be displayed in site waiting rooms, linked community pharmacies, and nearby educational institutions to share the study opportunity.3) Routine clinical practice: members of the clinical team can signpost potentially eligible patients to the study opportunity during routine consultations.

In strategy one, potential eligible patients will be identified at research sites through searching practice-based electronic healthcare registers using a standardised strategy. A practice clinician will screen the identified list of potentially eligible patients and exclude those ineligible. The remaining eligible patients, with a prior telephone check where appropriate, will be sent a text message and postal invitation from the practice signposting them to the study webpage, where the participant information sheet (PIS) and e-consent form can be found. A reminder will be sent after two weeks if no response. A simplified two-page PIS summarising what will be required from participants enrolled in the study will be made available on the study website.

Other potentially eligible patients may also be approached opportunistically by a member of the clinical care team in routine practice (strategy three). These patients and those who see the study advertised in the community around participating sites (strategy two) will be able to scan the study QR code to complete an online expression of interest. If deemed eligible for the study, they will be invited to consent into the study.

A convenience sample of GPs around England will be sought to complete an online survey. GP participants will be recruited through the professional networks and social media. GPs will have the option to be entered into a random draw for two £25 e-vouchers on completion of the survey. Young people participants who have given consent for interviews will be purposively sampled across practice location and deprivation and GPs who have delivered COPING at sites will be invited for interview and asked to e-consent. Both will be reimbursed for their time on completion of interviews.

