^. If we expect 50% to respond then n=50 would be sufficient to provide a margin of error no greater than 0.1 standard error (SE) around an estimate for a proportion based on a binary response item “e.g., would you be willing to participate in a future RCT of COPING (yes/no)”. Therefore, if 25/50 respond ‘yes’, it will generate an estimate of the proportion who answer positively of 0.5 (50%) with margin of error <= +/-0.1 relating to a z-value of +/-1.282 allowing a 90% 1-sided confidence interval (CI) and 80% 2-sided CI (providing sufficiently precise confidence interval estimation) around the observed estimate.

Nested qualitative study:

It is anticipated that a sample of around 16–20 participants (8–10 young people participants and 8–10 GPs) is likely enough to identify problems in COPING delivery and achieve data saturation, where data no longer offers new insights
^
27
^.

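### The interview plan leaves out trained site GPs who never delivered COPING and does not ensure that young people who missed the second consult are heard, so the two qualitative progression criteria may be biased favourably

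*Protocol article*

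**What the plan says.** The Recruitment section of the protocol article gives one entry rule for GP interviews: "GPs who have delivered COPING at sites will be invited for interview". No other group of GPs is named for interview. For young people the rule is: "Young people participants who have given consent for interviews will be purposively sampled across practice location and deprivation". Attendance and withdrawal are not among the sampling characteristics.

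The Sample size section plans "8–10 young people participants and 8–10 GPs" and says that this number "is likely enough to identify problems in COPING delivery and achieve data saturation".

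In Table 1 (Outcomes), the Go level for the delivery row reads "Delivery of COPING judged strongly feasible by qualitative data". The acceptability row is likewise decided on qualitative data, from both GPs and patients. The other five rows are percentages.

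Three further sections matter here:
- Recruitment also says that each site's principal investigator identifies the GPs who wish to deliver COPING, so these GPs are volunteers.
- Data collection methods says that GPs record second-consult attendance on the case report form. Statistical methods uses that attendance as the adherence measure.
- Qualitative analysis includes free text from the national GP survey alongside the interviews.

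**The concern.** The interviews are meant to bring delivery problems to light, yet a GP enters the frame only by having delivered. A site GP who completed the training and then never used COPING, whether for lack of time, confidence or suitable patients, may hold direct evidence of a delivery problem and is not invited. Selection happens twice: first GPs who want to deliver, then those among them who did.

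For young people the gap is softer. Whether someone came back for the second consult is the study's own measure of adherence and is likely to bear on how acceptable they found COPING. It is recorded but not used to choose interviewees. If non-attenders are less willing to be interviewed, few or none may be heard.

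At stake is the decision to move to a full RCT. A barrier that stops GPs from starting, or the reason why young people do not return, could be under-represented in the evidence for two of the seven criteria.

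**Working it through.** **The plan's own figures.** The interview sample of 16–20 has no formula, so there is nothing to reproduce. The 31 participants form the pool from which young people are interviewed, and that figure does reproduce. For the fidelity and adherence rows (Stop 40%, Go 67%; one-sided 5% alpha, 90% power):

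- n = (1.645·√(0.40·0.60) + 1.282·√(0.67·0.33))² / 0.27² = 27.2, which rounds up to 28.
- With continuity correction: (27.2/4)·(1 + √(1 + 2/(27.2·0.27)))² = 30.8, which rounds up to 31.

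Nothing in this point changes that number.

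**Young people.** Inputs: 31 recruited, 67% adherence (the Go boundary), 8–10 interviews. This gives 21 attenders (31 × 0.67 = 20.8) and 10 non-attenders. I treat the interviews as a draw without replacement from the 31, a simplification because the sampling is purposive and limited to those who consent to interview.

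With equal uptake, the chance of no non-attender is:
- 8 interviews: C(21,8)/C(31,8) = 203,490/7,888,725 = 2.6%.
- 10 interviews: C(21,10)/C(31,10) = 352,716/44,352,165 = 0.8%.

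For lower uptake I used the Wallenius non-central hypergeometric distribution. The documents give no uptake figure, so the odds ratios are assumptions, shown as a range:

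| Non-attenders' relative odds of interview | Expected non-attenders (8 / 10 interviews) | Chance of none (8 / 10 interviews) |
|---|---|---|
| 1 (equal) | 2.6 / 3.2 | 2.6% / 0.8% |
| 1/2 | 1.6 / 2.1 | 13% / 7% |
| 1/4 | 1.0 / 1.2 | 34% / 24% |

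At 40% adherence (19 non-attenders) with equal uptake, 4.9 of 8 or 6.1 of 10 interviewees would be non-attenders. The direction of any skew therefore depends on uptake and adherence, not on the sampling rule itself.

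**GPs.** Six sites with about three GPs each gives 18. If 31 participants fell at random among them (assumption), 18 × (17/18)³¹ = 3.1 GPs would deliver to nobody. This shows that the excluded group need not be empty. It does not measure barriers, because under this model those GPs received no participant by chance. The number actually prevented from delivering is unknown.

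**The case against.** A reader might infer that both criteria are judged mainly on cases in which delivery worked, and so are biased towards Go. The documents do not support that:

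- Having delivered COPING does not mean that delivery went well or was completed. A GP whose patient did not return, or who covered few checklist items, can still be invited.
- Young people who missed the second consult are eligible for interview. A shortage of them needs lower uptake, which is plausible but nowhere stated.
- Failure to return is a progression criterion of its own (adherence, Stop below 40%), and poor delivery lowers the fidelity criterion. Favourable interviews could not hide low attendance, and the Integration of data section plans to look for dissonance between sources.
- The survey asks GPs around England about barriers and enablers, and its free text enters the same thematic analysis. The qualitative evidence is therefore not confined to GPs who delivered.
- GPs who never used COPING cannot describe delivering it. With 8–10 GP interviews, giving priority to experience is defensible.
- The article is condensed, and finer sampling characteristics may stand in the full protocol.

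All of this limits the point without removing it. Adherence counts those who did not return but does not say why. A trained GP who takes on no participant adds nothing to the adherence or fidelity percentages. Survey respondents are a convenience sample reached through professional networks and social media, so they can report expected barriers, but the survey does not target trained site GPs or ask why one of them did not start. The condensed format explains silence on attendance, but the GP entry rule is stated outright.

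**Conclusion.** The point holds in a limited form. The GP part rests on the stated rule alone and needs no assumption: trained site GPs who never delivered are not invited, although the interviews are meant to find delivery problems. The young people's part is an omission, not an exclusion: "purposively sampled across practice location and deprivation" does not ensure that non-attenders are included.

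Both qualitative criteria may therefore be biased favourably, by an amount that the documents do not allow anyone to estimate. For young people, the chance of hearing from no non-attender runs from about 1–3% to 24–34% over the assumed uptake ratios, with 31 recruited and 67% adherence. No sample size or quantitative criterion is affected.

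**What to change.** In Recruitment, invite for interview all site GPs who completed COPING training, including those who delivered to no participant. For young people who consented to interview, add second-consult attendance or withdrawal from COPING to practice location and deprivation as purposive sampling characteristics. Keep the 8–10 interviews per group and set no fixed quota of non-attenders: no number can be derived from the documents, and a quota may be unattainable if adherence is high or few non-attenders agree.

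The cost is a change of wording, probably a minor amendment, with no extra interviews. Attendance is already on the case report form, and participants who withdraw from COPING are still invited to complete the follow-up questionnaires, so a contact route exists. The downsides are somewhat fewer interviews with deliverers and attenders, and non-attenders who may be harder to reach.
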